### Statistical analysis: exploratory endpoint—impact of male *Wolbachia-Aedes* deployments on the circulation of dengue serotypes and diagnosed secondary infections

Dengue test samples sent to the Environmental Health Institute will be further sent for serotyping and diagnosis of secondary infections as part of routine dengue surveillance based on the laboratory procedures described in the preceding sections. We will monitor trends in the circulation of specific dengue serotypes and secondary infection cases in intervention and non-intervention clusters, before, during, and after male *Wolbachia-Aedes* deployments have taken place. For assessing the serotype-specific efficacy of *Wolbachia-Aedes* deployments, we will employ a similar logistic regression strategy to estimate the intervention effect of male *Wolbachia-Aedes* by calculating the aggregate odds ratio, which compares the exposure odds among serotype-specific test-positive cases versus test-negative controls (see above).

For assessing the efficacy of *Wolbachia-Aedes* deployments on preventing secondary dengue infection, we will employ the logistic regression to estimate the intervention effect of male *Wolbachia-Aedes* by calculating the aggregate odds ratio, which compares the exposure odds among test-positive cases who are also flagged as secondary infections versus test-negative controls (see above).

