## Methods

### Overview

The aim of this study is to determine whether large-scale deployment of *Wolbachia*-infected male *Ae. aegypti* mosquitoes (the intervention, thereafter referred to as male *Wolbachia-Aedes*) can reduce the incidence of dengue in individuals living in intervention (treatment) clusters, compared to individuals living in non-intervention clusters. The two primary endpoints are (1) odds ratio of *Wolbachia* exposure distribution (i.e., probability of living in an intervention cluster) among laboratory-confirmed reported dengue cases compared to test-negative controls, and (2) laboratory-confirmed reported dengue case counts normalized by population size in intervention versus non-intervention clusters. Secondary endpoints include the efficacy of male *Wolbachia-Aedes* deployment in reducing *Ae. aegypti* mosquito populations, the impact of male *Wolbachia-Aedes* deployment on *Ae. albopictus* mosquito populations, and the pre-post trial community attitudes/knowledge and acceptance of male *Wolbachia-Aedes* and other vector control practices. Exploratory endpoints include the impact of male *Wolbachia-Aedes* deployment on the circulation of dengue cases of specific serotypes and on secondary infections.

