### Laboratory investigation

Diagnostic laboratories under the national dengue virus surveillance program use an internally controlled RT-qPCR assay, dengue non-structural protein 1 (NS1) or IgM as diagnostic assays to detect dengue virus in plasma samples from all dengue-suspected patients [44, 52, 53]. We will account for differences in the type of diagnostic tests used during data analysis. On a representative subsample of dengue-suspected patients sent to Environmental Health Institute, IgG in the serum samples will be determined by enzyme-linked immunosorbent assay (ELISA) using the Panbio Dengue IgG Indirect ELISA (Alere Inc., Waltham, Massachusetts). Quality assurance audits are regularly carried out in the laboratories

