### Case-control classification

Classification of dengue cases and dengue-negative controls is shown in Fig. 1. Dengue cases are patients with virologically confirmed DENV infection through RT-qPCR, testing positive for NS1 antigen or IgM, according to MOH’s criteria. A positive test for any of the three assays would classify the patient as a dengue case. Controls are patients with negative test results for DENV through RT-qPCR, NS1 antigen ELISA, or DENV IgM.

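### The secondary-infection odds ratio should take its controls from the same IgG-tested subsample as its cases, and should also be reported against IgG-positive controls (exploratory endpoint, minor)

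*Protocol article*

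**What the plan says.** The Overview lists the endpoint as exploratory: the impact of "deployment on the circulation of dengue cases of specific serotypes and on secondary infections". No power calculation is attached to it.

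The statistical section for this endpoint says that samples sent to the Environmental Health Institute will undergo "diagnosis of secondary infections as part of routine dengue surveillance based on the laboratory procedures described in the preceding sections". The model is a logistic regression that "compares the exposure odds among test-positive cases who are also flagged as secondary infections versus test-negative controls".

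Under Laboratory investigation, the diagnostic assays are RT-qPCR, NS1 and IgM. IgG is the only assay described there that could point to past infection, and it is limited in scope: "On a representative subsample of dengue-suspected patients sent to Environmental Health Institute", "IgG in the serum samples will be determined by enzyme-linked immunosorbent assay (ELISA").

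Under Case-control classification, "A positive test for any of the three assays would classify the patient as a dengue case", so a case may be confirmed by IgM only. "Controls are patients with negative test results for DENV through RT-qPCR, NS1 antigen ELISA, or DENV IgM". IgG plays no part in defining a control.

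Two other places set the principle for choosing controls. Study design argues that controls reproduce the exposure distribution of the source population that gave rise to the cases. The Discussion lists, as assumption (v) of the design, that controls come from all people at risk.

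**The concern.** The case group and the control group for this endpoint come from different populations in two respects.

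- **Sampling frame.** A flagged case must have been handled at the Institute and been eligible for IgG testing. A control can come from anywhere in the laboratory network, with or without an IgG result.
- **People at risk.** Someone never infected with dengue cannot have a secondary infection, yet such people are included among the controls.

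If the odds ratio is read as the effect of the releases on secondary infection in people who could have one, a between-arm difference in past exposure, or in the share of samples sent for IgG, enters it as a multiplier. With 15 clusters, and an allocation constrained only on the ratio of positive to negative dengue tests, neither quantity is assured to be equal between arms. What is at stake is the interpretation of one exploratory result.

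**Working it through.** The documents state no figure for this endpoint, so there is none to reproduce. The check is algebraic, followed by an illustration with assumed inputs.

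**Notation**, for arm a (1 = intervention, 0 = non-intervention):
- N_a: source population
- s_a: share previously infected
- r_a: risk of dengue among those previously infected
- f_a: fraction of samples that receive IgG, taken as equal for cases and controls within an arm
- RR = r_1/r_0: the effect among previously infected people

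IgG is treated as a correct marker of past infection, and care-seeking as the test-negative design assumes.

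**Step 1. Flagged cases.** Their number in arm a is proportional to N_a × s_a × r_a × f_a.

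**Step 2. Three choices of controls.**

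| Controls | Proportional to | Odds ratio estimates |
|---|---|---|
| All test-negative (as written) | N_a | RR × (s_1/s_0) × (f_1/f_0) |
| All test-negative in the IgG subsample | N_a × f_a | RR × (s_1/s_0) |
| IgG-positive test-negative in the subsample | N_a × f_a × s_a | RR |

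**Step 3. Equal arms.** If s_1 = s_0 and f_1 = f_0, all three give RR. A true 0.50 is reported as 0.50, whether prior exposure is 50% or 30% in both arms.

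**Step 4. Unequal prior exposure.** The documents say only that seroprevalence has fallen and give no value, so the levels here are assumed. With a true RR of 0.50 and equal f:
- 40% (intervention) vs 50%: 0.50 × 40/50 = 0.40
- 50% vs 40%: 0.50 × 50/40 = 0.63
- IgG-positive controls return 0.50 in both cases.

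**Step 5. A plausible chance difference.** Assume a between-cluster SD of 10 points, equal cluster weights and simple 8:7 allocation. The SD of the arm difference is 10 × √(1/8 + 1/7) = 10 × 0.518 = 5.2 points. For a one-SD difference:
- One arm at 50%, the other at 44.8%: 0.50 × 44.8/50 = 0.45, or 0.50 × 50/44.8 = 0.56.
- Centred on 50% (47.4% and 52.6%): 0.45 or 0.55.
- One arm at 30%, the other at 24.8%: 0.41 or 0.60.
- Cluster SD of 5 points (difference 2.6 points), one arm at 50%: 0.50 × 47.4/50 = 0.47, or 0.50 × 50/47.4 = 0.53.

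**Step 6. Unequal IgG sampling.** With equal s, and an assumed 20% of samples receiving IgG in the intervention arm against 25% in the other, the odds ratio as written is 0.50 × 20/25 = 0.40. Controls from the same subsample return 0.50.

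**The case against.** The strongest reply is that the comparator is legitimate. In a test-negative design the controls stand for the source population. Against all controls the odds ratio estimates the relative population incidence of secondary dengue, which is a valid quantity and parallels the serotype analysis in the same section. Choosing IgG-positive controls changes the target. Prior exposure is also balanced in expectation by randomisation, and the protocol already concedes that the number of clusters is small.

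Most of this stands. Including never-infected controls is not an error in itself. But the population-incidence reading also needs the IgG-sampled fraction to be equal between arms. Calling the subsample representative makes gross inequality less likely, but it does not state equal fractions by cluster. Balance in expectation also says nothing about the single allocation drawn, and IgG-positive controls remove this source of variation at little cost.

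A reader might go further and infer that secondary infection is flagged from IgG alone, so that first infections sampled late are counted as secondary. The documents do not support that. The endpoint section points to the laboratory procedures as a whole, which include RT-qPCR, NS1 and IgM. The flagging rule may sit in the full protocol, analysis plan or laboratory procedures, which are not shown. Even if some primary cases were flagged at the same rate in both arms, the odds ratio would move only if efficacy differed between primary and secondary infection. With q the true secondary share of non-intervention cases and m the share of primary cases flagged, the observed ratio is [q × RR_s + (1 − q) × m × RR_p] / [q + (1 − q) × m]. This equals 0.50 for every q and m when RR_s = RR_p = 0.50. Nothing in the documents indicates that the two differ.

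**Conclusion.** The point holds as a minor improvement to an exploratory endpoint. As written, flagged cases come from an IgG-tested subset and from previously infected people, while controls come from the whole network regardless of past infection. This departs from the plan's own principle that controls represent the population from which the cases arose.

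The distortion is the product of two between-arm ratios and vanishes when both are 1. Under the assumed 10-point cluster SD and prior exposure near 50%, a one-SD imbalance moves a true 0.50 to about 0.45 or 0.56. The movement is smaller with a 5-point SD and larger at lower seroprevalence. All of these inputs are assumptions, and the direction cannot be predicted. No primary or secondary endpoint is touched.

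**What to change.** In the statistical section for the exploratory endpoint:

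1. Draw the test-negative controls from the same IgG-tested subsample as the flagged cases.
2. Report the odds ratio against all controls in that subsample, read as the relative population incidence of secondary dengue. Alongside it, report the odds ratio against IgG-positive test-negative controls, read as the effect among previously infected people.
3. As a sensitivity analysis, repeat both with flagged cases confirmed by RT-qPCR or NS1, leaving out IgM-only cases, because IgG in those may come from the current infection.

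The IgG subsample is already drawn from dengue-suspected patients, which includes later controls as well as later cases, so the change is mainly one of wording. The cost is fewer controls, and fewer cases in the sensitivity analysis, hence wider intervals. The size of that loss cannot be computed because the article does not give the size of the subsample.

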### Trial governance and safety

The principal investigator, together with a Trial Steering Committee (TSC) comprising members from NEA, Singapore, and the Ministry of Health, Singapore, will be responsible for ensuring the study is performed in compliance with the approved protocol and the principles of Good Clinical Practice, and will also oversee the coordination of the trial process and data analysis for the trial. The TSC will meet quarterly or as needed throughout the trial. Day-to-day support for the trial, including production, releases, data management, and data analysis, will be overseen by a project team within NEA’s Environmental Health Institute, which meets monthly.

A Review Committee (RC) will be constituted from local and international experts external to the institutions involved in the trial. Its primary role is to ensure the safety and efficacy of the intervention during the trial, as well as overall compliance and conduct of the trial. The RC can provide recommendations to the TSC on continuing/discontinuing the trial and may also make recommendations to the TSC relating to trial procedures, protocol and data management, and quality control as well as analysis. Any proposed major changes to trial protocol will be reviewed by the RC, and approval for a protocol amendment will be sought from the relevant institutional review boards (IRBs) prior to their implementation. Responsibilities and terms of reference will be set out in an RC agreement and agreed to by all RC members prior to study commencement. The RC will meet at study initiation, at 6 months following the commencement of data collection, and at attainment of 50% of the estimated minimum required number of dengue tests (*n* = 1000), as well as any other time at the request of the TSC.

A Data Monitoring Committee (DMC) is not constituted due to the low-risk nature of the intervention. The trial is not considered human biological research, as advised by the Ministry of Health; all laboratory tests will be performed for clinically directed reasons; and data from these tests is routinely collected as part of routine dengue surveillance under the Infectious Diseases Act [46].

### Interim analyses and stopping rules

An interim analysis of the primary endpoints will be conducted when data collection reaches 25%, 50%, and 75% of the estimated minimum required number of dengue tests (*n* = 500, 1000, 1500). Upon interim analysis at the 50% mark, results will be communicated to the RC, and RC may recommend modification/termination of the study if data analysis shows that exposure to male *Wolbachia-Aedes* confers a reduced risk of dengue in the primary endpoints. We follow [44] and will employ the *p* < 0.01 cutoff at interim analysis to be used as guidance for considering early termination. RC may also recommend trial termination if preliminary results at the 50% mark suggest that male *Wolbachia-Aedes* deployments are associated with excess dengue incidence/cases. A less conservative *p* < 0.05 cutoff will be used as guidance for the latter, if results show that the association is in the direction of harm. Termination or modification may also be recommended for any other operational reason (e.g., data collection rates), perceived safety concerns, or external factors. The final decision to terminate or modify the study rests with the TSC.

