### Expected study duration

Deployment of male *Wolbachia*-*Aedes* and data collection from diagnostic laboratories is expected to commence in June 2022 (see Table 1). Data collection will continue for least 24 months or longer if needed to reach the minimum sample size required for intention-to-treat analysis. To account for year-to-year variability in dengue cases, data collection will continue for at least 24 months even if the estimated minimum sample size is attained sooner.

**Table 1 Tab1:** Trial timeline

Key activities	Period
Randomization	February 2022
Engage healthcare institutions for data collection [GPs, hospitals, polyclinics]	March 2022–June 2022
Phase 1 sentiment survey	March 2022–June 2022
Community engagement	June 2022 onwards
Start of RCT (releases at 8 intervention sites)	July 2022
Phase 2 sentiment survey	September 2022–December 2022
Phase 3 sentiment survey	December 2022–March 2023
End of RCT	September 2024
Final analysis	September 2024–November 2024
Publication of results	December 2024

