### Power calculations—first primary endpoint

It is estimated that 1600 test-negative controls and 400 dengue-positive cases will be needed to detect a 50% reduction in dengue incidence with 80% power. Sample size requirements will be re-estimated using observed data after attaining 50% of the target data collection.

We follow [44, 47, 54] to estimate the sample size for the proposed study design. We used the comparison of exposure odds among test-positive cases vs. test-negative controls for data aggregated across all clusters, with the null hypothesis that the odds of residence in a treatment cluster is the same among test-positive cases as test-negative controls [44, 47, 54]. This provides an unbiased estimate of the relative risk between groups as demonstrated previously [44, 47, 54].

We performed simulations (*n* = 1000) to estimate the power to detect a 50% intervention effect, assuming eight clusters per arm, and using available historical dengue testing data in the 15 study clusters. We randomly allocated eight clusters to receive the intervention; this random allocation was repeated 10,000 times, and allocations were only kept when constrained randomization criterion were met (*n* = 3151 possible balanced allocations). In each iteration of the simulation, we randomly selected one distinct intervention allocation and a 2-year time frame from the historical dengue testing data and simulated a 50% intervention effect in the intervention arm in the latter 12 months. The simulated data was analyzed using logistic regression to assess the significance of intervention effect. These were repeated for various dengue test sample sizes. We computed the proportion of significant results obtained in each scenario. This provided an estimate for the power of our study and the sample size required to obtain the respective power [44].

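### The p<0.01 guidance for stopping early for benefit does not leave a final 5% test intact, and the protocol does not say which looks can stop the trial or whether the 50% re-estimation may use the arm difference

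*Protocol article*

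**What the plan says.** Under Interim analyses and stopping rules the protocol article states: "An interim analysis of the primary endpoints will be conducted when data collection reaches 25%, 50%, and 75" per cent of the minimum number of tests, which it gives as 500, 1000 and 1500. The next step is tied to one look: "Upon interim analysis at the 50% mark, results will be communicated to the RC", and that committee (the external Review Committee) may then recommend changing or ending the study if the data show a reduced risk of dengue. For benefit the investigators "will employ the *p* < 0.01 cutoff at interim analysis to be used as guidance for considering early termination". For harm, "A less conservative *p* < 0.05 cutoff will be used as guidance for the latter". The cutoffs do not bind: "The final decision to terminate or modify the study rests with the TSC", the Trial Steering Committee.

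Two other sections bear on this. Power calculations—first primary endpoint says: "Sample size requirements will be re-estimated using observed data after attaining 50% of the target data collection". It does not say whether the observed arm difference may enter. Expected study duration says: "Data collection will continue for least 24 months or longer if needed to reach the minimum sample size", and adds that the 24 months apply even if the minimum is reached sooner, so the final count can exceed 2000.

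The article gives no significance level for the final test and no overall type I error rate.

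**The concern.** A constant interim cutoff uses up some of the type I error. How much depends on how many looks can lead to an efficacy claim and on how strongly each look is correlated with the final test. At three looks, or even at one, 0.01 is not strict enough for the final test to stay at a full 0.05. The protocol fixes this boundary but leaves open the number of looks it applies to.

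The 50% point also carries two decisions at once: a possible stop or modification based on the arm comparison, and a re-estimation of sample size. If the re-estimation responds to the observed arm difference and the final test is then done naively, the error rate rises further.

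At stake is an efficacy claim, either early with p just under 0.01 or at the end with p just under 0.05, reported at an error rate that the procedure does not have. The trial is non-blinded and has no Data Monitoring Committee, so the numerical boundary is one of its safeguards.

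**Working it through.** **Inputs from the protocol.** 400 cases + 1600 controls = 2000 tests (Power calculations—first primary endpoint). Looks at 25%, 50% and 75%; benefit cutoff 0.01 (Interim analyses). Minimum 24 months (Expected study duration). 722,204 residents and 51-621 reported cases per 100,000 a year (Study setting).

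**Assumptions.** Final test two-sided 0.05; interim cutoffs two-sided; guidance followed when crossed; a test that is valid when done once; information proportional to tests; no data-driven change in size.

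**Step 1: the plan's own figure.** 0.25, 0.50 and 0.75 × 2000 = 500, 1000 and 1500. This agrees with the protocol.

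**Step 2: model.** Under the null, the statistics at information fractions s < t have correlation √(s/t). Critical values are 2.576 (p = 0.01), 1.960 (0.05) and 3.291 (0.001).

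**Step 3: final analysis at 2000 tests.**
- Only the 50% look can stop: correlation √0.5 = 0.707. P(cross at look) = 0.0100, P(cross at end) = 0.0500, P(both) = 0.0054. Overall = 0.0100 + 0.0500 − 0.0054 = 0.0546.
- All three can stop: first-crossing probabilities 0.0100 + 0.0077 + 0.0060 + 0.0382 (final) = 0.0619.
- A simulation of 4 million null trials gives 0.0546 and 0.0619.
- Counting only false claims of benefit, against a nominal 2.5%: 2.73% and 3.10%.

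**Step 4: final count above 2000.** Over 24 months, national rates in the study population would give 722,204 × 0.00051 × 2 = 737 to 722,204 × 0.00621 × 2 = 8,970 cases. That is 1.8 to 22 times the 400 required, assuming national rates, full capture and no effect. Looks fixed at 500, 1000 and 1500 then fall earlier and correlate less with the final test.

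| Final count ÷ 2000 | 50% look only | All three looks |
|---|---|---|
| 1 | 5.46% | 6.19% |
| 1.5 | 5.64% | 6.59% |
| 2 | 5.72% | 6.77% |
| 5 | 5.86% | 7.06% |
| 10 | 5.91% | 7.16% |

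**Step 5: persistent between-cluster variation.** Let τ be the persistent between-cluster variance as a multiple of the final within-cluster variance. The effective information fraction at test fraction t becomes (τ + 1)/(τ + 1/t). For the 50% look this is 2/3 = 0.67 with τ = 1 and 4/5 = 0.80 with τ = 3, rather than 0.50. A simulation of 3 million replicates with a cluster-adjusted test gives 5.3% and 5.1% with one look, and 5.8% and 5.4% with three. The protocol gives no value for τ.

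**Step 6: alternatives.**
- Looks at p<0.001, final test at 0.05. With 2000 tests the overall rate is 0.0502 (one look) or 0.0508 (three); with 20,000 it is 0.0509 or 0.0523.
- Looks kept at 0.01. The final level that restores 0.05 at 2000 tests is 0.0452 (one look, z = 2.003) or 0.0366 (three looks, z = 2.090). Solving the same equation for 4000 tests gives 0.0425 or 0.0308, so the level has to be recalculated if more tests accrue.

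**The case against.** The strongest case against has five parts.

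1. **No final level is stated.** A reader might infer that the final test is fixed at an unadjusted 0.05, so that the error rate certainly exceeds 5%. The document does not say so, and an analysis plan that is not shown may set an adjusted level. This stands: every rate here is conditional. The interim boundary itself, however, is stated, and it determines what the final level must be.

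2. **Three stopping looks is not the best-supported reading.** Communication to the Review Committee and stopping for benefit or harm are described for the 50% mark. Trial governance and safety likewise schedules a committee meeting at 1000 tests and none at 500 or 1500. This largely stands, so the one-look figure is closest to the text. But the cutoff is worded for interim analysis in general, and nothing excludes stopping at the other two looks.

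3. **The re-estimation may be harmless.** A reader might infer that it is driven by the observed effect and attach a further inflation figure. No conditional-power rule or cap appears in the document. It is equally natural to read the passage as repeating the power simulation on observed data with the 50% target kept. No size can therefore be given; the point is only that the arm difference is not excluded.

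4. **The model is simplified.** With 15 fixed clusters, persistent between-cluster variation ties the looks more closely to the final test and lowers the excess (step 5). The second primary endpoint is powered by months of follow-up (31), so a model in test counts does not describe it. Both stand, and the figures are limited to the test-negative endpoint.

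5. **The cutoff is guidance and not the only protection.** External experts on the Review Committee see the 50% results, and major protocol changes go through that committee and ethics review. This stands too: the rates describe what happens if the guidance is followed.

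**Conclusion.** The point holds as a modest, conditional one. If the final test is at two-sided 0.05 and the guidance is followed, p<0.01 at the 50% look alone gives about 5.4-5.5% for the test-negative endpoint, or 5.6-5.9% if the final count goes well above 2000. If all three looks can stop the trial, the rate is about 6.2%, or 6.6-7.2% with a larger final count. These figures assume information proportional to tests, and persistent between-cluster variation would bring them down. Re-estimation on the observed effect would add an amount that the document does not allow anyone to compute. The documents do not establish that the final test is unadjusted, that all three looks can stop the trial, or that the re-estimation uses the effect. The excess ranges from about half a point to two points, which justifies an inexpensive change and does not put the design in doubt.

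**What to change.** 1. State which of the three looks can stop the trial for benefit.

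2. Replace the 0.01 benefit cutoff with p<0.001, which keeps the overall rate at about 0.050-0.052 with the final test at 0.05, whichever looks can stop the trial and for every final count checked. An O'Brien-Fleming-type spending function would also serve. If 0.01 is kept, set the final level at about 0.045 (one stopping look) or 0.037 (three), recalculated at the actual information fractions if the final count exceeds 2000.

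3. Restrict the 50% re-estimation to arm-blind quantities (pooled test positivity, accrual, between-cluster variation ignoring arm), with the 50% target effect kept.

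4. Leave the harm guidance as it is.

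**Cost.** A change of wording and no extra data. Early stopping for benefit needs stronger evidence. Under the model above, with a true effect giving exactly 80% power (drift 1.960 + 0.842 = 2.802), the expected z at the 50% look is 2.802 × 0.707 = 1.981. The chance of crossing there falls from Φ(1.981 − 2.576) = 0.28 to Φ(1.981 − 3.291) = 0.10. If that loss is unwelcome, keeping 0.01 avoids it at the price of a slightly stricter final threshold.
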